### Procedure

Psychiatrists, psychologists, or psychiatric nurses will check their caseload for patients who meet the requirements for participation and ascertain whether they are interested in participating. If this is the case, the researcher will provide an information letter. The patient will be given 7 days to read the letter and to decide whether he/she wants to participate. At a second appointment, the researcher will check whether the patient has understood the information in the letter. Subsequently, both parties sign an informed consent form in twofold. Randomization is performed by an independent external agency.

## Measurements and instruments

There are four moments of assessment over the course of 2 years. The baseline assessment takes place before MBT-P is started. Furthermore, there will be an assessment after 9 months (halfway MBT-P), after 18 months (directly after MBT-P has ended), and after 24 months (6 months after MBT-P has ended). See Table 1 for the specific instruments that are used at each assessment.

**Table 1 Tab1:** Overview of the different instruments at each measurement moment

	Intake	T0: Baseline measurement (0 months)	T1: Halfway Measurement (9 months)	T3: End of Treatment (18 months)	T4: Follow-up (24 months)
CASH	X				
SFS		X		X	X
TAT		X		X	X
ESM		X	X	X	X
HT		X		X	X
MANSA		X		X	X
MAQ		X	X	X	X
DSFM		X			
PANSS		X		X	X
GDQ		X			
CECA		X			
GAF		X		X	X

### Diagnosis

All patients are diagnosed according to DSM-IV criteria [45] by a psychiatrist. Prior to participation, this diagnosis will also be verified using the Comprehensive Assessment of Symptoms and History (CASH). The CASH is a semi-structured interview that documents signs, symptoms, and history of psychotic, manic and depressive syndromes as well as substance abuse. The instrument has been extensively tested concerning interrater reliability, test-retest reliability and validity [46].

### Social functioning

Social functioning is measured using the Social Functioning Scale (SFS), a self-report questionnaire. The SFS has been found to be reliable, valid, sensitive, and responsive to change [47]. The scale contains seven dimensions of global social functioning that are especially pertinent to patients suffering from psychotic disorders. The dimensions are: social withdrawal, interpersonal communication, independence (competence), independence (performance), recreational activities, social activities, and employment.

Secondly, using the modified GAF scale [48], global functioning will be assessed. The modified GAF scale is a clinician or researcher-rated instrument, which makes it a good addition to the self-reported SFS. It has more detailed criteria and a more structured scoring system than the original GAF, which is underscored by a high interrater reliability.

### Social cognitive capacity

It has been pointed out that there is to date no agreement on the assessment of social cognition, but there is a broad consensus that it is a multifaceted construct [49]. In the current study, social cognition is therefore assessed with two instruments that measure different aspects of social cognition: the Thematic Apperception Test (TAT) and the hinting task (HT). The TAT [50], scored with the Social Cognition and Object Relations System (SCORS) [51], is used to assess four dimensions of social cognition: complexity of representations of people and understanding of social causality, which comprise cognitive aspects of social cognition, and the affect-tone of relationships and the capacity for emotional investment, comprising affective aspects of social cognition. Each dimension is scored on a 5-point scale, with higher scores representing higher social cognitive functioning in that dimension. Six pictures of the TAT are used. TAT responses are recorded and transcribed verbatim. TAT responses, when analyzed with the SCORS, have been found to be a valid and reliable way to measure social cognition and object relations [52, 53]. According to Luyten and colleagues [54], the TAT is one of the few tests that takes almost all aspects of mentalization into account, including affective and cognitive aspects.

The HT [37] is used to measure the ability to infer intentions from others, or ‘Theory of Mind’ (ToM). Patients read extracts that describe an interaction between two characters in which one character says something with an implicit message. If the patient infers the implicit message correctly, two points are scored. If a hint is needed, a score of 1 is given. When the answer is incorrect or the participant does not know, 0 points are scored. The test comprise ten short passages. The Hinting Task has very recently been reviewed [55] regarding test-retest reliability, utility as a repeated measure, relation to functional outcome, and internal consistency and was one of two tests shown with strong psychometric properties across all evaluation criteria.

### Social stress reactivity

Emotional reactivity to stress in social situations is measured with an electronic diary using the ‘Experience Sampling Method’ (ESM) [56]. ESM is a repeated self-assessment technique with great ecological validity. Participants carry around an ESM device, which facilitates the monitoring of daily life experiences and behavior. Ten times daily on five consecutive days, it generates an audible signal (beep) at unpredictable moments of the day which participants answer by using the touch screen of the device. Participants are asked whether they are alone or in company of others. Then, both the level of social stress and negative/positive affect are assessed. Social stress is measured with items such as: “I would rather be alone” and “I like the present company” (reverse coded). Negative affect is the averaged score of the mood items “anxious”, “lonely”, “insecure”, “irritated”, “down”, “guilty”, and “gloomy”. Positive affect will be measured with the items “happy”, “satisfied”, “cheerful”, “relaxed”, and “enthusiastic”. All items are scored on a 7-point Likert Scale.

### Quality of life

Using the Manchester Short Assessment of quality of life (MANSA) [57], changes in overall quality of life are measured. The MANSA is a 16-item, 7-point Likert-scale self-rating instrument.

### Psychotic symptom severity

Interviewers use the Positive and Negative Syndrome Scale (PANSS) [58] to assess positive (subscale P), negative (subscale N), anxious (item G2), and depressive symptoms (item G4). The PANSS is a 30-item, 7-point Likert-scale rating instrument developed for the assessment of phenomena associated with schizophrenia. A Dutch version is used [59].

Additionally, the ESM diary is used to measure momentary psychotic experiences. Seven ESM items are used: ‘I feel suspicious’, ‘I am afraid of losing control’, ‘I feel that others don’t like me’, ‘I feel that others want to hurt me’, ‘My thoughts are influenced by other people’, ‘I feel unreal’, and ‘I hear voices’.

### Awareness of having a mental disorder

The PANSS (item G12) is used to assess awareness of having a mental disorder.

### Substance abuse

Patients are asked to report substance use on the ESM device at each beep using categorical questions. Patients will report whether they have used any substance since the last beep, including: (1) caffeine, (2) nicotine, (3) medication, (4) alcohol, (5) cannabis, (6) other drugs, or (7) none.

### Personality organization/somatization of psychopathology

Assessment of personality organization and the tendency to somatize severe psychopathology is conducted using theory driven profiles of the Dutch short Form of the MMPI (DSFM) [60], an 83-item self-assessment questionnaire. The DSFM measures personality traits on 5 scales: Extraversion, Psychopathology, Shyness, Somatization, and Negativism. Using the theory driven profile approach to the DSFM [61–65], five levels of Personality Organization (PO) are distinguished: Neurotic PO, Borderline PO, Narcissistic Borderline PO, Latent Psychotic PO and Manifest Psychotic PO. To measure bodily awareness, the DSFM “Somatization” subscale (20 items) will be used. This subscale measures the amount and degree of experienced bodily symptoms, and hence, the ability to subjectively report, and be aware of bodily sensations. As described [65] affect regulation through somatization will be expressed as the relative position of scores on the subscale somatization to that on the severe psychopathology subscale.

### Childhood trauma

The Childhood Experience of Care and Abuse (CECA) [66] is a semi-structured interview that aims to assess details and the time-sequence of traumatic childhood experiences. It assesses lack of care (neglect, antipathy), physical abuse, sexual abuse, and psychological abuse.

### Adherence to drug treatment

Each patient’s medical record is consulted to ascertain the pharmacotherapy prescribed at t0, t1, t2, and t3. Adherence to the prescribed medication is measured with the Medication Adherence Questionnaire (MAQ) [67].

### Adherence to the MBT-model

Adherence to the MBT model by therapists is rated by an experienced MBT therapist according to the MBT adherence and competence scale [68], using footage of therapy sessions. Therapists are judged on 17 items that characterize proper MBT treatment.

### Duration of illness

Assessed using the CASH, refers to the period since first psychosis.

### General demographics

The general demographic questionnaire (GDQ) is a standard instrument used in all ESM studies conducted at Maastricht University. It documents treatment history, socio-economic status, educational level, and urbanicity of the place of residence.

### Treatment

#### TAU

All patients in the current study receive a multifaceted treatment based on the ‘Functional Assertive Community Treatment’ (FACT) model. FACT teams consist of psychiatric nurses, welfare workers, psychologists, and at least one psychiatrist. The intervention consists of pharmacotherapy, case-management, psycho-education, and in some cases cognitive behavioral therapy (CBT). CBT interventions for psychosis usually take around 20 sessions and are based on the work of van der Gaag [69, 70]. Whether or not patients have received CBT, and how many sessions, will be registered and taken into account.

Furthermore, all patients will receive supportive-structuring therapy. Sessions focus on problems patients may encounter in their social network, work, daily activities, or medication adherence. Patients meet with a mental health professional for an average of 30 min every 2 weeks, with a minimum of 1 meeting of 30 min per month, over 18 months. The total number of individual sessions is estimated to be around 30 (15 h of individual therapy). Adherence to treatment sessions is monitored by registering patients’ presence in the sessions.

#### MBT-P

Patients in the TAU plus MBT-P condition receive the same treatment mentioned above in combination with individual and group MBT-P. The key elements of MBT, shortly described below, provided the basis for MBT-P [16].

#### Therapeutic stance

MBT is characterized by the ‘not knowing stance’ in which the therapist admits to not knowing what the patient experiences. By actively asking questions the therapist cultivates an attitude of sincere interest in the patient. This gives the patient the experience of being ‘kept in mind’ by someone, but also stimulates curiosity in the patient towards his own mental states.

#### Interventions

When applying interventions, it should always be kept in mind that arousal tends to diminish the capacity to mentalize. Four stages of intervention can be used in a step-wise manner, depending on the level of arousal. At the first level, interventions are aimed at down-regulating arousal in the patient. These include empathic validation of the patient’s feelings and complimenting good mentalizing. At the second stage the therapist asks for clarification of a situation or elaboration on the patient’s feelings and thoughts. Often the therapist stops or rewinds the patient’s narrative to investigate an aspect of the dialogue. This stage is about making implicit mentalizing explicit. Often details are investigated that seem to affect the patient, or should affect the patient, but do not. This then leads to the next stage, called ‘mentalized affectivity’, which is the activity of reflecting on emotions, while simultaneously experiencing them. It is considered to be a crucial aspect of emotion regulation. The explicit mentalizing of a primary affective experience gives the patient the opportunity to express (or inhibit) emotions in a non-automatic manner. At the last stage, the relationship between therapist and patient or between patients is mentalized. In this stage, both patient and therapist reflect on and share their affective experience to become aware how their relationship is affecting them. Care should be taken applying this stage of intervention, as it requires a robust level of mentalizing.

#### Duration and dose

Compared to original MBT, the length of MBT-P, has remained unchanged: 18 months. However, the frequency and length of sessions has been reduced. In our experience, based on a pilot MBT-P intervention, NAPD is associated with more severe mentalizing deficits than BPD, as has also been suggested elsewhere [71]. Given, the danger of overwhelming NAPD patients with mentalizing interventions, group therapy is limited to weekly 1-hour sessions, while individual therapy takes place in biweekly half-hour sessions. We feel this approach is justified by the low drop-out rate of 10 % in the pilot intervention.

#### Psycho-education

MBT-P starts with two sessions of psycho-education, in which patients are told about the key aspects of MBT, including the meaning of mentalizing and its sensitivity to arousal.

#### Individual therapy

Individual therapy provides an opportunity for intensive practice in mentalizing. The focus is on establishing a secure relationship that acts as a safe base from which failures in mentalizing can be explored. Treatment goals on the basis of five problem areas are developed and routinely reviewed with the patient, including: commitment to treatment, psychiatric symptoms, social interaction/relationships, destructive behavior, and community functioning.

#### Group therapy

Since patients with NAPD tend to experience a great deal of stress in social situations, group therapy provides an opportunity to practice mentalizing in a stress-evoking setting. Group therapy can also generate a sense of belonging and attachment that help foster mentalizing. The group size is a maximum of eight patients and there will be one MBT-P therapist and one co-therapist present at each session.

#### Therapists

Group therapists are experienced and registered MBT therapists. Individual therapists are mental health professionals (psychologists, psychiatric nurses or psychiatrists) who receive training to become MBT-P therapists. Supervision is provided in weekly sessions of up to 1h, during which therapists reflect on their interventions and whether they are faithful to the MBT model.

### Statistical analysis

#### Main effect

The main purpose of the statistical analysis is to compare the overall effect of treatment condition on social functioning. For this, an ANCOVA will be used with treatment condition as between-subjects variable, post-treatment social functioning as dependent variable, and baseline social functioning as a covariate. Other potential covariates include childhood trauma, level of PO, somatization of psychopathology, medication use, attendance of MBT-P sessions, duration of illness and adherence to the MBT-model by therapists. Similar analyses will be conducted for the secondary outcome measures (social cognition, quality of life, awareness of having a mental disorder, anxious, depressive, negative and positive symptoms and substance abuse).

Since drop-out will undoubtedly result in missing data, the possibility of attrition-bias is a cause of concern [72]. For example, it is conceivable that those who fare the worst in therapy tend to drop out, thus creating a biased sample. Following the advice of Altman [73], the analyses will therefore be conducted on the basis of ‘intention to treat’ (ITT), meaning that they will include all patients who sign up, regardless of actual participation in the entire program. Missing data will be handled by means of multiple imputation (MI) [74]. In the current case missingness is most likely to be caused by participants dropping out of their respective treatment programs. Since certain variables have been found to influence drop-out rates in patients with NAPD, we cannot assume that the data are missing at random. A review [75] identified a lack of insight, poor social functioning, positive symptoms, young age, male gender, a history of drug abuse, and unemployment as key predictors of treatment program drop out. Thus in the current study, these variables will be used to predict missingness. Additionally, treatment condition will be used as a predictor as well, because the time investment differs between conditions. For each analysis, a total of 5 imputed datasets will be created using a fully conditional Markov chain Monte Carlo (MCMC) approach, which will be combined using standard procedures [76].

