### Covariates

Certain potential effect modifiers will be taken into account. First, adverse childhood experiences such as neglect or physical, psychological, and sexual abuse have been associated with social dysfunction later in life [40]. Second, personality organization (PO) has been shown to impact psychotherapy treatment response [41] and the level of social cognition [42]. Five levels of personality organization (PO) are identified, each characterized by different levels of anxiety tolerance and different capacities for impulse inhibition or ‘control’: Neurotic PO (good anxiety tolerance, over-control); Borderline PO (moderate to poor anxiety tolerance, differing levels of control); Narcissistic Borderline PO (good anxiety tolerance, undercontrol); Latent Psychotic PO (moderate anxiety tolerance, weak control); and Manifest Psychotic PO (poor anxiety tolerance, weak control). Third, the awareness of bodily sensations has been regarded as the first level of emotional awareness [43], which is an essential part of social cognition [44]. Psychopathology usually is accompanied by (vague) physical complaints, called “somatization”. A failure to report physical complaints while suffering (severe) psychopathology may be indicative of an absence of bodily awareness and therefore an impaired social cognitive capacity. Fourth, medication use can affect social functioning in patients with NAPD, therefore the type of medication is registered and adherence to medication is measured. Fifth, MBT attendance is taken into account, because it is expected that those who attend more sessions will profit more. Sixth, baseline measurements of the outcome variables will be accounted for. Seventh, the duration of illness, because of its negative impact on functioning; and eighth, adherence to the MBT model by therapists, because it is likely to influence treatment outcome.

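### The main-effect ANCOVA is sound at its core, but MBT-P attendance and therapist adherence, which exist only in the MBT-P arm after randomisation, are offered as covariates for it without restriction

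*Protocol article*

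**What the plan says.** Under Statistical analysis, Main effect, the purpose is to "compare the overall effect of treatment condition on social functioning". The model is given in full: "an ANCOVA will be used with treatment condition as between-subjects variable, post-treatment social functioning as dependent variable, and baseline social functioning as a covariate". The next sentence opens "Other potential covariates include childhood trauma, level of PO" and goes on through somatization to "medication use, attendance of MBT-P sessions, duration of illness and adherence to the MBT-model by therapists". Similar analyses are announced for the secondary outcomes. No separate place is given for attendance or therapist adherence, and no value is defined for TAU patients.

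The Covariates section introduces the same variables with "Certain potential effect modifiers will be taken into account" and gives the reason for attendance: "MBT attendance is taken into account, because it is expected that those who attend more sessions will profit more". Therapist adherence is included there because it probably influences outcome.

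Two other sections fix what these variables are. Trial design/setting says that only one arm receives MBT-P. Adherence to the MBT-model says that adherence is rated from recordings of therapy sessions, so during treatment.

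**The concern.** A covariate in a randomised comparison should be fixed before allocation or be unaffected by it. Attendance of MBT-P sessions and adherence to the MBT model are neither: they come into being because a patient was allocated to MBT-P, and a TAU patient has no such value. Attendance is also expected, on the article's own reasoning, to be the route by which patients benefit. Adjusting for it can therefore subtract the effect that the trial was set up to measure.

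Every simple way of handling the TAU arm causes trouble. Coded 0, the variable nearly duplicates the treatment indicator. Left missing, a complete-case ANCOVA loses the whole TAU arm and the treatment effect cannot be estimated. Imputed, the analysis uses values that do not exist. At stake is whether the treatment coefficient still answers the question set for it, and whether the planned sample can detect an effect.

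**Working it through.** **Inputs from the article (Sample size calculation).** Effect 0.7 SD; alpha 0.05 (two-sided assumed, since 68 is reproduced only that way); power 0.80; baseline-to-post correlation 0.40; 40 + 40 recruited; 25% drop-out leaving 60.

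**Inputs assumed.** Attendance in MBT-P as a share of sessions, mean 75% and SD 20%, capped at 0 and 100%, coded 0 in TAU; alternatives below. The article gives no attendance distribution.

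**1. The plan's own figures.** An exact two-sided t-test at d = 0.7 has 79.97% power with 33 per arm and 81.2% with 34, hence 68 in total. Baseline adjustment gives (1 - 0.4²) × 68 = 0.84 × 68 = 57.12, hence 58. Drop-out leaves 80 × 0.75 = 60. Power with 30 per arm is about 83%. All of this assumes adjustment for baseline SFS only.

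**2. What the coefficient becomes.** Let τ be the overall effect, μ the mean attendance in MBT-P and γ the slope of outcome on attendance within that arm. With TAU coded 0, the adjusted treatment coefficient is τ - γμ, the effect extrapolated to zero attendance.
- Benefit proportional to attendance: γ = τ/μ, so the coefficient is 0.70 - 0.70 = 0.
- Constant benefit: γ = 0, so the coefficient stays 0.70, but precision is lost.
- No effect, attendance correlated c with prognosis: γ = c√0.84/SD. The coefficient is -c × 0.917 × 0.75/0.20, which is -0.69 at c = 0.2 and -1.03 at c = 0.3, before the cap at 100%.

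**3. Precision.** The variance inflation for treatment is 1/(1 - μ²/(2·SD² + μ²)) = 1/(1 - 0.5625/0.6425) = 8.0, so the SE rises about 2.8-fold. From √(0.84 × 2/30) = 0.24 it reaches about 0.67; the cap narrows the spread of attendance, and simulation gives about 0.74.

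**4. Simulation, 30 per arm, with and without attendance.**

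| Scenario | Baseline SFS only | Plus attendance (TAU = 0) |
|---|---|---|
| Benefit proportional to attendance | coefficient about 0.7, power 81% | coefficient about 0, power 5% |
| Constant benefit | coefficient 0.7, power 82% | coefficient 0.7, power 16% |
| No effect, c = 0.2 | bias 0, type I error 5% | bias about -0.76 SD, type I error 17% |
| No effect, c = 0.3 | bias 0, type I error 5% | bias about -1.1 SD, type I error about 33% (32% in a repeat run) |

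**5. Range over other attendance distributions** (mean/SD 0.7/0.2, 0.8/0.1, 0.6/0.3). With proportional benefit, power is 4% to 5% throughout. With half of the benefit proportional, the coefficient is 0.31 to 0.36 and power 5% to 13%. With constant benefit, the SE is 0.44 to 1.44 and power 7% to 34%. Adding therapist adherence as well (assumed to vary over five groups, mean 0.75, SD 0.15) takes the SE to about 1.1 to 1.8 and power to 5% to 10%.

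**6. A coding that avoids the distortion.** With attendance centred within the MBT-P arm and TAU set to 0, the coefficient returns to 0.70 with SE 0.24, power is about 82%, and under no effect the bias is 0 with type I error of 5% to 6%.

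**The case against.** The strongest reply is that the article commits to nothing harmful. The named model contains only treatment and baseline SFS, the sample size rests on that model, and the other variables are called potential. The harm follows only if they are entered, and only under some codings; coding and the final covariate set commonly belong in an analysis plan that is not shown. This stands as a limit on the point: it would be wrong to say that the randomised comparison is lost as planned. It does not remove the point. The article names two unsuitable variables for the main-effect model, with no restriction and no protective coding, which is a stated choice and not an omitted detail.

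A reader might infer more from the text, and these readings are not supported:
- *That the covariates contradict intention to treat.* The article uses that term for which patients are analysed, and a covariate excludes nobody. The conflict is with the stated aim of an overall effect.
- *That CBT sessions are in the model.* The TAU section says "Whether or not patients have received CBT, and how many sessions, will be registered and taken into account", but CBT is not in the ANCOVA list.
- *That on-study medication will be adjusted for.* The list says only medication use, and prescriptions are recorded at t0 as well as later, so a baseline value exists.
- *That effect modification will be sought with additive terms only.* The article does not say whether interactions will be fitted.
- *That the primary model can be picked after seeing results.* The lack of a selection rule is detail that an analysis plan may supply.

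**Conclusion.** The point holds in limited form. The core ANCOVA is right for its purpose, but attendance of MBT-P sessions and therapist adherence should not be available to it as covariates. Entered with TAU coded 0, they change what the treatment coefficient estimates and leave the trial with little power. The false-positive risk that they create runs against MBT-P when patients with better prognosis attend more. The direction of these results follows from the algebra; their size rests on the assumed attendance distribution, the 0 coding and the attendance-prognosis correlation, none of which the article gives.

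**What to change.** 1. Strike attendance of MBT-P sessions and therapist adherence from the covariates of the main-effect ANCOVA and of the similar analyses of secondary outcomes.
2. Limit any covariate beyond baseline SFS to prespecified baseline variables, using the t0 value for medication.
3. Analyse attendance and therapist adherence only in analyses labelled exploratory: within the MBT-P arm, or, for attendance, by a complier-average analysis.

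The cost is a change of wording and a small amount of extra exploratory analysis. No new data are needed, and the sample size calculation then matches the model.

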## Research aims and hypotheses

### Primary research aim

The primary aim of this study is to establish whether mentalization-based treatment for psychotic disorder (MBT-P) improves self-reported social functioning in patients with NAPD. We hypothesize that patients who receive MBT-P will show greater improvements in social functioning compared to patients who have had treatment as usual (TAU) only. We also expect that any difference observed will still be present at a 6 month follow-up.

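### The protocol says the data cannot be assumed missing at random, then names only an imputation method that needs that assumption, and fixes just 5 imputations

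*Protocol article*

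**What the plan says.** Three statements in the Main effect subsection of the protocol article's Statistical analysis bear on this point.

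- **Assumption and its reason.** "Since certain variables have been found to influence drop-out rates in patients with NAPD, we cannot assume that the data are missing at random". The text then lists predictors of drop-out (insight, social functioning, positive symptoms, age, gender, drug-abuse history, unemployment). It says that these, together with treatment condition, will be used to predict missingness.
- **Feared mechanism.** The text says "it is conceivable that those who fare the worst in therapy tend to drop out, thus creating a biased sample". It offers intention to treat and multiple imputation in response.
- **Method.** For each analysis "a total of 5 imputed datasets will be created" by a fully conditional MCMC approach, pooled in the standard way. The article names no other missing-data method.

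Table 1 schedules the SFS, the primary outcome, at baseline, 18 months and 24 months. The 9-month assessment has only the experience sampling diary (ESM) and the medication adherence questionnaire. The Sample size calculation gives a baseline to post-treatment correlation of 0.40. It expects drop-out above the pilot's 10% without giving a rate, and checks that 60 of 80 patients would remain if 25% were lost.

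**The concern.** The stated premise and the chosen method do not fit together. Standard multiple imputation gives valid inference when missingness depends only on quantities that are observed and in the model. That is MAR, which the text says it cannot assume. The reason given does not support the denial either: known, recorded predictors of drop-out argue against missing completely at random, and using them in the model is how one makes MAR plausible.

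The mechanism that would break MAR is the other one the section raises, drop-out driven by how the patient is doing under treatment. The remedy offered does not reach it. A patient who deteriorates and leaves before 18 months has a single SFS value, at baseline, so the deterioration cannot be seen on the primary scale.

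Separately, with 5 imputations the pooled estimate and its standard error carry visible simulation noise. At stake are a correctly stated assumption behind the primary result, some check on the bias the authors themselves fear, and a p-value that a second analyst could reproduce.

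**Working it through.** **1. The plan's own figures.** Inputs from the Sample size calculation: d = 0.7, alpha 0.05, power 0.80, correlation 0.40, N = 80.
- Two-sided t-test (noncentral t): 34 per arm, 68 in total, power 0.81. This matches.
- ANCOVA factor: (1 − 0.40²) × 68 = 0.84 × 68 = 57.1, rounded up to 58. This matches.
- After 25% loss: 80 × 0.75 = 60, which is above 58; ANCOVA power with 60 patients is about 0.83.

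Nothing below changes these figures.

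**2. The assumption.** Set the parts of the argument side by side.
- Premise: "Since certain variables have been found to influence drop-out rates in patients with NAPD".
- Conclusion drawn: "we cannot assume that the data are missing at random".
- Action: put those variables and treatment in the imputation.

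The premise excludes missing completely at random, and the action is the usual one under MAR. Only the conclusion is out of line.

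**3. What the baseline SFS can tell the imputation.** With correlation 0.40, baseline explains 0.40² = 16% of the variance of the 18-month score. No later SFS exists for a patient lost before 18 months. The 9-month diary may carry some indirect information.

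**4. Size of the feared bias (illustration only).** Large-sample simulation with true d = 0.70, correlation 0.40, 25% missing, and a log-odds slope of 0.9 per SD wherever drop-out depends on a score. The slope and the mechanisms are assumptions; the protocol gives none. Imputation from treatment and baseline gives:

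| Drop-out depends on | Estimated effect |
|---|---|
| Baseline and arm (MAR) | 0.70 |
| Outcome relative to own arm's mean, alike in both arms | 0.71 |
| Absolute outcome score | 0.64 |
| Outcome, in the MBT-P arm only | 0.88 |

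The error can be nil, downward or upward. More imputations do not remove it.

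**5. Five imputations: efficiency.** Relative efficiency is 1/(1 + FMI/m), where FMI is the fraction of missing information. The protocol gives no FMI, so 0.10 to 0.40 is assumed.
- FMI 0.10, m = 5: 1/1.02 = 98.0%
- FMI 0.25, m = 5: 1/1.05 = 95.2%
- FMI 0.40, m = 5: 1/1.08 = 92.6%
- FMI 0.25, m = 50: 1/1.005 = 99.5%

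**6. Five imputations: repeatability.** The Monte Carlo SD of the pooled estimate, in standard errors, is √(FMI/m). At FMI 0.25 this is √0.05 = 0.22 for m = 5 and √0.005 = 0.07 for m = 50.

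A simulation shows what this does to the primary test. It uses 40 patients per arm, d = 0.7, correlation 0.40, equal random loss in both arms, Bayesian linear imputation from treatment and baseline, ANCOVA, and Rubin's rules with small-sample degrees of freedom. There were 30 reruns per simulated trial, with 1,500 trials at m = 5 and 500 at m = 50. The probability that two reruns on the same data fall on opposite sides of p = 0.05 is:

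| Missing | m = 5 | m = 50 |
|---|---|---|
| 10% | 4.3% | 1.1% |
| 25% | 11.7% | 2.9% |

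The mean FMI in these runs was about 0.12 and 0.27. With a true effect of 0.55, which is not the protocol's value, the m = 5 figure at 25% missing rises to about 15%.

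**The case against.** The strongest reply is that this is one wrong phrase. The authors evidently meant missing completely at random. They list the right kind of predictors, include treatment, and impute under MAR, so correcting the wording leaves the procedure as it is. That largely stands, and it is why a reader should not infer that the primary analysis is invalid or rests on an assumption its authors reject. What the correction does not settle is the outcome-related drop-out that the section raises itself.

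A second reply is that a sensitivity analysis may sit in an analysis plan that is not shown. That also stands: its absence from an article is no finding in itself. The point is narrower. The article states a specific threat and pairs it with a remedy that does not meet it.

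Third, 5 imputations lose little efficiency, and the instability shrinks as loss falls. That is correct; the defect is repeatability, not validity.

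Several further inferences are tempting but not supported:
- **That 25% loss is expected.** The figure is a what-if allowance; no expected rate is given.
- **That the effect will be overstated.** This needs an arm-specific mechanism that nothing in the protocol documents.
- **That later SFS scores or other outcomes are barred from the imputation model.** The article lists predictors of missingness, not a closed model.
- **That therapy leavers will not be assessed.** The text says only that "missingness is most likely to be caused by participants dropping out of their respective treatment programs", and visits are scheduled by month with no condition on staying in therapy.
- **That patients who were never randomised would be analysed.** The phrase "they will include all patients who sign up, regardless of actual participation in the entire program" is loose, but consent leads on to randomisation in the Procedure section.

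Adding a 9-month SFS would be a design preference, not the repair of an error.

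**Conclusion.** The point holds in limited form. The stated missing-data assumption is wrong for the method named and for the reason given, most likely through confusion with missing completely at random. The bias that the section itself fears is not answered by intention to treat plus MAR-based imputation, unless the decline is captured in observed data. Its size and direction cannot be derived from the documents; the illustrative range of 0.64 to 0.88 around a true 0.70 rests wholly on assumed mechanisms.

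The fixed number of imputations costs about 2% to 7% in efficiency over FMI 0.10 to 0.40. It makes a borderline result depend on the seed: about 12% disagreement between reruns at the 25% allowance and about 4-5% at 10% missing, against 1-3% with 50 imputations. These rates assume d = 0.7, correlation 0.40 and imputation from treatment and baseline only.

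This should be fixed before analysis. It is not a must-fix matter, because correcting the sentence leaves a standard and defensible primary procedure.

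**What to change.** 1. Replace the sentence on the assumption. State that data are assumed missing at random given the listed drop-out predictors and treatment condition, and that missing completely at random is not assumed.
2. Raise the number of imputations from 5 to about 50, and record the random seed.
3. Prespecify a delta-adjusted (tipping-point) sensitivity analysis for the primary outcome. The shift applied to imputed 18-month SFS scores should be allowed to differ between arms, to show how much worse unobserved patients would have to be before the conclusion changes. If an unpublished analysis plan already contains this, a reference to it is enough.

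The cost is a few sentences, some extra analysis work and a little computer time. Patient burden, visits and every sample-size figure stay as they are.
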